#### Adverse Events

All adverse events (AEs) and adverse events following immunization (AEFI) occurring during the study will be recorded and monitored as per ICH-GCP (2016) (21) and ICMR guidelines (17). Safety would also be assessed in case of all withdrawals. All adverse events will be recorded and meticulously followed till resolution. Serious adverse events will require immediate reporting by the study investigator to the Sponsor and Ethics Committee, within 24 h, of becoming aware of the SAE. All Adverse Events will be classified by the study physician and recorded in the AE form. Any symptoms recorded on COVID-Kavach App will be immediately followed by investigators to rule out COVID-19. The Data Safety Monitoring Board (DSMB) will be formed to monitor safety of the participants and assess safety data. Clinical assessments and lab investigations will be carried out as per Tables 1, 2.

#### Concomitant Medication

As a general principle, concomitant medication of any kind will be kept to a minimum and will necessarily require clearance from a primary care physician and with full information provided to the study physician. All concomitant medication will be recorded in the study case record form (CRF) by the study physician. All complete CRFs/eCRF duly signed by the investigator and counter signed by principal investigator will be submitted within 2 weeks of the completion of the study to the Chief Clinical Coordinator. Although the study includes healthy participants, the medication required for any new illness during the study will be taken under supervision of the primary care physician and meticulously recorded in the participant CRF. Participants will be permitted general symptomatic medications like paracetamol and non-steroidal anti-inflammatory drugs for short period (<4 days) and including for any untoward mild to moderate symptoms like headache and body aches following vaccination. Patients will be carefully explained not to consume any other herbal and home remedies. Patients will be advised not to use any kind of food and nutrition supplement. Similarly, participants will be advised not to consume any kind of vitamins and/or minerals without a specific advice of physician.

### Statistical Analysis

#### Sample Size and Power

The sample size is calculated based on the primary objective of improved immunogenicity of the vaccine with administration of Ashwagandha. Also, it was felt important to obtain a reasonably suitable (non-probabilistic) sample size for safety and tolerability. As there was no prior data on the expected effect size of the difference between the two study groups, a superiority margin of 7% was decided by expert consensus between the biostatistician (SS) and senior authors (AC, GT, [name], and BP). The sample size was calculated with 80% power and after consideration of interim analysis at the end of 12 weeks; assuming vaccine efficacy of 80% (22). The calculated sample size with the provision of one interim analysis was rounded to 600 subjects per study arms and totalling 1,200. The study will include upto 300 participants who have received the first dose and at least 900 participants who have received the second dose.

An interim analysis is planned after completing 12 weeks of intervention. The sample size of the study is decided based on the plan of one interim analysis. The sample size for interim analysis will be minimum 300 (with alpha = 2.96%).

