**Methods and Analysis:**

We designed a prospective, randomized, double-blind, parallel-group, placebo-controlled, two-arm, exploratory study on healthy volunteers receiving the COVISHIELD^TM^ vaccine. The administration of Ashwagandha will begin within 7 days of the first or second dose of COVISHIELDTM. Primary outcome measure is immunogenicity as measured by SARS-CoV-2 spike (S1) and RBD-specific IgG antibody titres. Secondary outcome measures are safety, protective immune response and quality of life measures. All adverse events will be monitored at each time throughout the study. Participants will be tracked on a daily basis with a user-friendly mobile phone application. Following power calculation 600 participants will be recruited per arm to demonstrate superiority by a margin of 7% with 80% power. Study duration is 28 weeks with interim analysis at the end of 12 weeks.

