#### Clinical Outcomes

##### Primary Outcome Measure

Immunogenicity as measured by SARS-CoV-2 spike (S1) and RBD-specific IgG antibody titres.

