#### Analysis

A standard statistical software package will be used for statistical tests (parametric and non-parametric). The analysis will be both intention-to-treat (ITT) and as per-protocol (PP). All randomized participants will be included in the safety analysis. All statistical processing will be performed using standard statistical package (SPSS, BMDP, and CIA) unless otherwise stated. The data will be individually analyzed for central tendencies (mean, median), range, standard deviation and 95% confidence intervals for each intervention arm in the study. Titer data will be “log” transformed before any analyses [and GMT, GSD, etc. will be reported and will be used for testing with respect to that parameter. Data will be tabulated and graphically shown using standard format using MS Excel and other software programs. Standard parametric (Student *t*-tests–paired and unpaired, ANOVA, etc.) and non-parametric statistical tests (Wilcoxon Signed Rank test, Mann-Whitney “U” test, Kruskal-Wallis test, etc.) will be used depending upon the normality of the data, level of measurement and appropriateness/applicability. Fisher's exact test or Chi square will be used to test the proportion of participants classified as efficacy failures and those with AE. All AEs will be presented as proportion and with Wilson's recommended exact binomial 95% Confidence Interval.

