Previous clinical studies have highlighted the role of humoral as well as cell-mediated immune responses in recovery from SARS-CoV-2 infection (26, 27). In previous studies the selective-Th-1 upregulating activity of Ashwagandha was demonstrated and in infection models, co-administration of Ashwagandha with DPT vaccine resulted in improved antibody titres against lethal challenge of pertussis toxins (8). *In silico* network ethnopharmacological investigations also suggest the ability of bioactive compounds of Ashwagandha to modulate immune pathways involved in innate and adaptive immune responses (28, 29). Further, the interim efficacy data for ChAdOx1 nCoV-19, evaluated in four trials across UK, Brazil and South Africa shows a protection of 64.1% after one standard dose (14). COVISHIELD^TM^ has been administered in two doses to a large population in India. We hypothesize that co-administration of Ashwagandha with the COVISHIELD^TM^ vaccine may enhance the antibody titres particularly after the first dose of the vaccine. A sustained long-term immune response to the vaccine has implications for prevention of reinfection. Therefore, the effect of Ashwagandha on the sustenance of neutralizing antibody titres up to 4 months after the second dose will also be evaluated in this study (30). Ashwagandha is also known to improve overall mental wellbeing.

Currently, the study involves the assessment of neutralizing antibodies against two well-characterized variants of concern (B1.617.2 and USA-WA1/2020 variants). Recently, a new variant B.1.1.529, named Omicron has emerged and it is likely that other newer variants may emerge during the course of the study. It would be interesting to evaluate the responses to these variants. As and when fully characterized BEI resources are available for new variants of concern, the investigators will take the decision to modify and make the necessary amendments to the protocol. Serum samples are being preserved at all time points of the study and may be used for such additional studies.

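### The stated 80% power belongs to a 7-point difference in a proportion near 80%, not to the IgG titre comparison that is the primary outcome

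*Protocol article*

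**What the plan says.** The Sample Size and Power section opens with its basis: "The sample size is calculated based on the primary objective of improved immunogenicity of the vaccine with administration of Ashwagandha". The Primary Outcome Measure section defines that objective: "Immunogenicity as measured by SARS-CoV-2 spike (S1) and RBD-specific IgG antibody titres". Under Analysis, titres are log-transformed, and the geometric mean and geometric SD are reported and "will be used for testing with respect to that parameter".

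The inputs to the calculation are of another kind. Because there were no prior data on the size of the difference, "a superiority margin of 7% was decided by expert consensus". The size was "calculated with 80% power and after consideration of interim analysis at the end of 12 weeks; assuming vaccine efficacy of 80" per cent, and the result was rounded to 600 per arm, 1,200 in all. The only significance level given is tied to the interim look: "The sample size for interim analysis will be minimum 300 (with alpha = 2.96" per cent). The abstract names IgG titre as primary and then states that "600 participants will be recruited per arm to demonstrate superiority by a margin of 7% with 80% power".

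Breakthrough infection, RT-PCR-confirmed COVID-19 and percent seroconversion are listed as secondary outcomes. None is given an expected rate.

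**The concern.** The section claims one endpoint and calculates for another. A comparison of log titres needs an SD and a target GMT ratio, and neither appears. An 80% rate and a 7% difference are inputs for comparing two proportions, and the primary outcome is not a proportion.

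The 80% does not describe an event in this trial either. Vaccine efficacy is a relative reduction in risk against unvaccinated people. Both arms are vaccinated, so neither arm will show an 80% rate of anything the plan names as primary.

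The headline power figure is at stake. The abstract puts the 80% power close to the IgG outcome, so a reader will attach one to the other. The documents supply no power for that comparison.

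**Working it through.** **Inputs from the protocol article.** Power 80%, vaccine efficacy 80%, margin 7%, alpha 2.96% (stated for the interim) and 600 per arm, from Sample Size and Power; 1:1 allocation, from Randomization. Not stated: final alpha, sidedness, formula, SD of log titre, target GMT ratio.

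**Step 1: reproduce 600 per arm.** Treat 80% as a proportion p used for the variance in both arms, and 7% as an absolute difference d:

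n = 2p(1 − p)(z_α + z_β)² / d²

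For two-sided alpha 2.96%, z_α = 2.175; for 80% power, z_β = 0.842; the sum is 3.017.

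n = 2 × 0.80 × 0.20 × 3.017² / 0.07² = 0.32 × 9.102 / 0.0049 = 594.4, so 595 per arm.

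That fits a figure rounded to 600. Power at 600 per arm on the same formula: SE = √(0.32/600) = 0.0231; 0.07/0.0231 = 3.031; 3.031 − 2.175 = 0.856, which gives 80.4%.

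Using 2.96% for the full sample is an inference, since the text attaches it to the interim. At two-sided 5% the same formula gives 513.

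**Step 2: what the 80% power refers to.** Every number in Step 1 concerns a proportion near 80% and a 7-point difference, and none concerns a titre. The power for the log-titre comparison cannot be derived from the document.

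**Step 3: what 600 per arm can detect on the primary scale.** For a two-sample comparison of log10 titres, the difference detectable with 80% power is

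δ = (z_α + z_β) × SD × √(2/600), and the GMT ratio is 10^δ.

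With √(2/600) = 0.0577, δ is 2.802 × 0.0577 = 0.162 SD at two-sided 5%, and 3.017 × 0.0577 = 0.174 SD at 2.96%. The document gives no SD, so the values below are assumed.

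| Assumed SD (log10) | GMT ratio, alpha 5% | GMT ratio, alpha 2.96% |
|---|---|---|
| 0.3 | 1.12 | 1.13 |
| 0.4 | 1.16 | 1.17 |
| 0.5 | 1.20 | 1.22 |
| 0.6 | 1.25 | 1.27 |

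For SD 0.5 at 5%, for example: δ = 0.162 × 0.5 = 0.081, and 10^0.081 = 1.20.

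**The case against.** The best defence is that the arithmetic is sound and the section is open about its limits. The 600 follows from the stated inputs, the lack of prior data and the use of expert consensus are disclosed, and the abstract calls the study exploratory. All of that stands. It does not close the gap: a lack of prior data explains choosing an effect by consensus, but not choosing it on a different scale from the endpoint. The same abstract that says exploratory also claims powered superiority.

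It might also be said that the 80% stands for a rate of immune response. No titre-responder endpoint is defined, however. Seroconversion is secondary and has no expected rate, and the text calls the 80% vaccine efficacy.

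Several stronger readings are tempting, and the documents do not support them:

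- *The 600 is miscalculated.* A reader who sets 80% against 87% with unpooled variance gets 438 per arm at two-sided 5%, or 508 at 2.96%. That is a different formula, not an error in the plan; Step 1 gives 595.
- *The 7% is a margin to be exceeded, so a true 7-point gain could not succeed.* The section brings in the 7% because the expected effect size was unknown, and 600 reproduces when it is used as the expected difference. The word margin is loose.
- *The assumed efficacy is contradicted by the Discussion.* The single-dose figure there ("shows a protection of 64.1% after one standard dose") sits beside 76% after one dose in the Introduction, and at least 900 of the 1,200 participants enter after the second dose. Neither figure is a rate in a trial arm.
- *The trial is underpowered for titres or for infection.* The first is not shown by anything in the document. The second would rest on assumed attack rates for outcomes that are secondary.

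**Conclusion.** The concern holds as a mismatch of endpoint, not as an arithmetic error. The 80% power is for a 7-point difference in a proportion near 80%, which is not the primary endpoint. The plan states no power for the IgG titre comparison, although it says the size was based on it.

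The sample itself may well be adequate: 600 per arm detects about 0.16 SD (alpha 5%) or 0.17 SD (2.96%) on the log scale with 80% power. The GMT ratios in the table rest on the assumed SDs, on two-sided tests, and on one titre with a usable sample from all 600 participants in each arm. The plan states no final alpha, so both levels are shown.

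**What to change.** Keep 1,200 participants. In the abstract and in Sample Size and Power, remove the vaccine-efficacy basis and the claim of superiority by a 7% margin. Replace them with wording such as:

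*The null hypothesis is a GMT ratio of 1. With 600 participants per arm and 80% power at a two-sided final alpha of [value to be named], the detectable GMT ratio is [1.20 at alpha 5%; 1.22 at alpha 2.96%] if the SD is 0.5 log10. Over an assumed SD range of 0.3 to 0.6 log10 it is [1.12 to 1.25; 1.13 to 1.27]. The trial is not powered for breakthrough infection.*

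The final alpha must be named before one set of figures is chosen. The source of the SD range should be given or the range marked as assumed, and an allowance for lost samples should be stated. Because the sample size is already set, the ratio should be presented as what the trial can detect and not as a target effect chosen in advance.

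The cost is text in two places. Enrolment, visits and assays do not change. What is given up is a power claim that does not apply to the primary outcome.

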#### Randomization

The participants eligible for enrolment will be randomized in a 1:1 ratio to Ashwagandha + COVISHIELD^TM^ or placebo + COVISHIELD^TM^ according to a pre-specified randomization scheme prepared by a statistician (SS) using a computerized system. Block randomization specific to each clinical study site will ensure equal number of participants per group with a small block size (e.g., a block of 4–6 participants). The statistician (SS) will design the randomization schedule following computer generated random numbers. The randomization scheme will consider the subsets of participants who are receiving first and second dose.

The patient number and the treatment allocation as per the schedule will be printed on a card, which will be sealed in an opaque envelope for each patient. The envelope of each patient will be delivered to respective trial sites. The treatment allocation will be concealed. Considering the study design, it is important to have a dosage form that ensures blinding. The tablets of Ashwagandha and placebo will have identical color and weight and will be dispensed in sealed bottles. The bottles will have same color and labeling. The bottles will be specific to the participant. The participant code will be written on each bottle containing the tablets.

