Our trial has the potential to have a significant impact on current vaccination program by improving immunogenicity, protection and general wellbeing with simple, safe and affordable intervention. In this trial we expect a beneficial effect beginning soon after the first dose of vaccination. We hope to investigate biological plausibility that the immune protection offered by a long-term co-administration of Ashwagandha may effectively address some of the vexing issues associated with the vaccination.

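### First-dose hypothesis: at most 300 of 1,200 participants can inform it, and only an overall 600 v 600 comparison is sized, so an estimate by entry-dose group should be pre-specified

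*Protocol article*

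**What the plan says.** **Where the effect is expected.** The Discussion hypothesises that co-administration "may enhance the antibody titres particularly after the first dose of the vaccine". The Introduction raises the same idea as something of interest to investigate. The text after Table 2 in Study Design directs the 12-week interim analysis at safety and immune response following the first dose.

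**Who is recruited.** Sample Size and Power, and Recruitment, Screening, Consent before it, set the mix: "The study will include upto 300 participants who have received the first dose and at least 900 participants who have received the second dose". Tablets start within 7 days of whichever dose brought the participant in (Trial Intervention).

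**What is sized.** The calculation rests on the overall aim of improved immunogenicity. The result was "rounded to 600 subjects per study arms and totalling 1,200". The abstract puts it as "600 participants will be recruited per arm to demonstrate superiority by a margin of 7% with 80% power".

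**How entry dose is used.** Under Randomization: "The randomization scheme will consider the subsets of participants who are receiving first and second dose". The Analysis section lists candidate tests and log-transformed titres by arm. It does not mention entry dose. The primary outcome is S1 and RBD-specific IgG titre, with no entry-dose group named.

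**The concern.** Second-dose entrants had their first dose before they took any tablets, so their samples carry no information on whether Ashwagandha raises titres after the first dose. They make up at least 900/1,200 = 75% of the trial. The hypothesis that the Discussion singles out can be examined only in the capped group, and no size or power is stated for that group.

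The two entry groups also differ in exposure. First-dose entrants may receive their second dose while on tablets; for second-dose entrants no further vaccine dose is described. An overall arm difference averages two effects that may not be alike. A null overall result could conceal a first-dose effect, and a positive one would not show in which group the benefit arose.

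**Working it through.** **Inputs from the protocol.** 600 per arm, 1,200 in total, allocated 1:1. First-dose entrants number at most 300, so about 150 per arm and a share f = 300/1,200 = 0.25. Margin: "a superiority margin of 7% was decided by expert consensus". Reference rate: "assuming vaccine efficacy of 80" per cent. Power is 80%. Alpha of 2.96% is stated for the interim; sidedness and the final alpha are not given.

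**Assumptions.** Two-sided tests, 7% read as absolute points on a proportion, no dropout, equal variance in both entry groups, and exactly 150 and 450 per arm.

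**1. The plan's own figure.** With both rates at 80% and alpha 0.0296:

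n = 2 × 0.8 × 0.2 × (2.175 + 0.842)² / 0.07² = 594.4, so 595 per arm, which rounds to 600.

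This is one reading that fits. An ordinary comparison of 80% v 87% gives 441 (alpha 0.05) or 511 (alpha 0.0296). On any of these readings it is one two-arm calculation that is not split by entry dose.

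**2. Dilution on the log-titre scale.** Let d be the effect in first-dose entrants, r·d the effect in second-dose entrants, and s the SD.

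- Standard error (SE), first-dose entrants only: s√(2/150) = 0.1155s
- SE, overall: s√(2/600) = 0.0577s, which is half
- Overall effect: (0.25 + 0.75r)d
- Ratio of overall z to first-dose-only z: 2(0.25 + 0.75r)

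In the extreme case r = 0, the overall effect is 0.25d and z is halved. Power = Φ(z/2 − 1.96):

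| First-dose-only power | z | Overall power |
|---|---|---|
| 80% | 2.80 | Φ(−0.56) = 28.8% |
| 90% | 3.24 | Φ(−0.34) = 36.7% |

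Break-even: 0.25 + 0.75r = 0.5, so r = 1/3. Above one third the overall test is the stronger; at r = 1 its z is twice the first-dose-only z.

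**3. The same on the plan's 7-point scale, r = 0.** The overall difference is 0.25 × 7 = 1.75 points (80% v 81.75%).

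| Two-sided alpha | Overall, effect only in first-dose entrants | First-dose entrants alone, 150 v 150 | Same 7 points in all, 600 v 600 |
|---|---|---|---|
| 0.0296 | 8% | 29% | 86% |
| 0.05 | 12% | 37% | 91% |

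Here z is 0.77 overall against 1.64 in first-dose entrants, a ratio of 0.47.

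**4. The cap.** 300 is a maximum. With 150 first-dose entrants (assumed), f = 0.125 and the z ratio at r = 0 is √0.125 = 0.35.

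**5. What first-dose entrants can show.** The protocol gives no titre SD, so a range is assumed. Detectable log10 difference at 80% power, alpha 0.05 = 2.80 × SD × √(2/150):

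| Assumed log10 SD | Detectable GMT ratio |
|---|---|
| 0.4 | 1.35 |
| 0.5 | 1.45 |
| 0.6 | 1.56 |

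A ratio of 1.45 in first-dose entrants with no effect in the rest would appear overall as 1.45^0.25 = 1.10.

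**6. The interaction.** Its SE is s√(2/150 + 2/450) = 0.133s, against 0.1155s for the first-dose effect itself, so it is estimated less precisely still.

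**The case against.** Several points on the other side stand.

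- **Pooling is not written down.** The Analysis section never defines the primary model, and entry dose is considered at randomisation. A reader might infer that the final test ignores entry dose. The document does not say so; it follows only from the single sizing, and an analysis plan that is not shown may stratify.
- **The first-dose question is not the primary hypothesis.** The one in the Introduction covers long-term administration with the vaccine and names no dose. It is tempting to say that the trial fails to answer the question it puts first, but that goes too far. Nor do all the passages say the same thing: only the Discussion hypothesises a particular first-dose effect, and its later sentence, "In this trial we expect a beneficial effect beginning soon after the first dose of vaccination", concerns onset.
- **Dose-specific evaluation is partly present.** The interim is aimed at the first-dose response, and the secondary outcomes include seroconversion by vaccine dose and infection proportions for each dose period. However, the protocol does not say that the interim minimum of 300 is the first-dose group. If it is, power for 7 points is still about 29% at alpha 0.0296.
- **An effect confined to first-dose entrants is a worst case.** The text does not exclude an effect after the second dose, and above the one-third break-even the overall test is the better one.
- **A positive overall result need not come from second-dose entrants.** It simply does not show which group produced it. No passage says that it would be used to claim a first-dose effect.

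What survives is narrower. The cap and the single sizing are protocol decisions that no analysis plan can undo, and an overall comparison cannot separate the first-dose effect.

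**Conclusion.** The point holds as a mismatch between a stated hypothesis and the comparison that was sized, not as an error in the primary analysis. At least 75% of the sample cannot inform the first-dose hypothesis, and no size or power is given for the at most 150 per arm who can. If the final test is the overall comparison, the worst case leaves a quarter of the effect and half the z of a first-dose-only test (80% power to about 29%). These figures assume equal variances, the full 300 first-dose entrants and no effect in second-dose entrants. With fewer first-dose entrants the dilution is greater; with a second-dose effect above one third of the first-dose effect, pooling gains power. Power on the titre scale cannot be fixed from the document, because no SD is stated. This is a low-cost improvement that would let the trial speak to its own hypothesis.

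**What to change.** 1. Keep the overall 600 v 600 comparison, stratified by the entry-dose subsets considered at randomisation.
2. Pre-specify the S1 and RBD GMT ratio with 95% CI within each entry-dose group, together with the treatment-by-entry-dose interaction.
3. State that any conclusion about the response after the first dose rests on first-dose entrants only, using scheduled samples drawn before each participant's own second dose. Do not define this by fixed weeks 4 and 8: no dose interval is stated, the Secondary Outcome Measures allow the second dose before week 12, and visits have a 7-day window. The medication log under Compliance covers vaccine use, so it should supply the date.
4. Say openly that precision in this group is limited (detectable GMT ratio about 1.35 to 1.56 at 80% power, for an assumed log10 SD of 0.4 to 0.6, with the full 150 per arm), and more so for the interaction.

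The cost is analysis wording. S1 and RBD IgG are already scheduled at every visit from Day 1, so no new samples or participants are needed. The drawback is a wide interval for first-dose entrants, wider still if fewer than 300 are enrolled or if few samples precede the second dose.
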